The primary exposure is active enrolment onto the MCTS. Referral alone will not constitute exposure, as not all referred patients commence telehealth monitoring. For enrolled patients, the index date will be defined as the date on which active telehealth monitoring begins. To account for temporal variation in healthcare utilisation and service delivery, telehealth enrolment dates will be grouped into calendar quarters (Q1: January–March; Q2: April–June; Q3: July–September; Q4: October–December). Comparator patients will be selected from quarterly eligibility snapshots comprising individuals who were eligible for MCTS, alive, and registered during the same quarter but who did not enrol onto the service. Calendar quarter will be used as an exact matching variable within the propensity score matching process, ensuring that telehealth participants are compared only with eligible non-enrolled patients observed during the same time period. Additional demographic, clinical, risk, and baseline healthcare utilisation variables will be incorporated into the matching procedure. This approach aims to minimise temporal bias arising from changes in healthcare utilisation, seasonal pressures, COVID-19 recovery effects, admission practices, and service delivery over the study period. The primary analysis will therefore estimate the effect of active enrolment onto MCTS compared with eligible non-enrolment during the same calendar quarter. Findings should be interpreted as representing the effect of the telehealth service model as delivered in routine practice rather than the effect of referral alone or any individual intervention component.

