### Analysis

The study uses two quasi-experimental methods: IPTW-DiD and RD designs. These methods help to reduce the risk of selection bias due to systematic differences between those receiving and not receiving the intervention, in two ways.

The primary approach of the analysis is IPTW-DiD, which is specifically designed to adjust observed differences by reweighting individuals according to their probability of receiving treatment, thereby approximating a pseudo-population in which treatment is independent of observed confounders. The treated cohort will comprise patients who received telehealth, with treatment timing defined by the first quarter in which telehealth was received; patient-quarter observations from this quarter onwards will be considered post-intervention. For untreated patients, comparable index quarters will be assigned to define the pre- and post-intervention periods.

The initial analytic cohort will be restricted to patients aged 50 years or above with at least one relevant long-term condition linked to the telehealth packages: COPD, diabetes, or HF. These eligibility criteria will be applied to both treated and untreated patients to ensure that the control group comprises individuals with a realistic probability of receiving the intervention. To avoid interpreting unobserved quarters as zero healthcare utilisation, the initial analysis will use a balanced panel of patients observed in all 24 quarters across the 6-year study period. The potential selection introduced by excluding patients who die, move away, or register with a GP partway through the study period will be explored in sensitivity analyses.

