A treatment model will calculate the likelihood of each patient receiving the intervention using baseline socio-demographic variables, comorbidity measures, and 12-month cumulative pre-intervention healthcare utilisation, such as unplanned emergency admissions. For variables that may change over time, baseline or pre-intervention values will be used. Stabilised IPTW weights (Austin and Stuart, 2015) will be used in the DiD model to balance measured baseline covariates and reduce the influence of extreme weights. Covariate balance, weight stability, overlap/common support, effective sample size, and the plausibility of the conditional parallel-trends assumption will be assessed using weighting diagnostics and pre-intervention outcome trends. Comprehensive sensitivity analyses will be performed to evaluate the robustness of all estimates.

To manage the potentially large untreated population, the above eligibility restrictions will be applied before weighting. If the remaining comparison cohort is still too large for the available computing environment, a 5:1 propensity-score matched comparison cohort based on baseline characteristics may be constructed before applying the weighting approach; this will be reported as a computational sensitivity analysis.

Additionally, the RD design (Thistlethwaite and Campbell, 1960) will serve as a secondary complementary analysis, subject to the availability of a documented Johns Hopkins ACG risk score eligibility threshold (NHS England, 2025d) and sufficient observations close to that threshold. Threshold values, temporal changes, and geographical variations will be documented. As RD estimates a local effect among patients close to the eligibility threshold, its findings will be interpreted alongside, rather than as direct confirmation of, the IPTW-DiD estimates.

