Furthermore, the subgroup analyses will be carried out to investigate heterogeneity in the impact of the telehealth intervention across socio-demographic groups. Depending on the size of the subgroup and the availability of data, these analyses will be conducted within the main IPTW-DiD framework using either stratified models or interaction terms. Age, sex, ethnicity, chronic health conditions, frailty score, IMD quintiles, and geographical locations are among the suggested subgroups. For each subgroup, propensity score models and weighting diagnostics will be re-evaluated to ensure appropriate balance. The RD subgroup analyses will be conducted only where there is sufficient sample size close to the eligibility threshold (NHS England, 2025d).

**Work package 2:**  *To determine whether patients using Mersey Care Telehealth Service report improvements in quality of health, mental health, satisfaction, and wellbeing, and whether this varies by sociodemographic group or service delivery type*

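### The Work package 1 computing fallback (5:1 propensity matching, then weighting) is not a like-for-like variant of the primary IPTW-DiD, and no primary estimate is defined if it is triggered

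*Protocol article*

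**What the plan says.** The Work package 1 Analysis section makes inverse probability of treatment weighted difference-in-differences (IPTW-DiD) the primary approach. It describes this as "reweighting individuals according to their probability of receiving treatment, thereby approximating a pseudo-population in which treatment is independent of observed confounders". The treatment model is built "using baseline socio-demographic variables, comorbidity measures, and 12-month cumulative pre-intervention healthcare utilisation, such as unplanned emergency admissions". Stabilised weights "will be used in the DiD model to balance measured baseline covariates and reduce the influence of extreme weights".

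The same section then adds a contingency. Its trigger is "If the remaining comparison cohort is still too large for the available computing environment". Its content is that "a 5:1 propensity-score matched comparison cohort based on baseline characteristics may be constructed before applying the weighting approach". Its status is that "this will be reported as a computational sensitivity analysis". The text does not say which propensity score produces the weights in the matched set, nor whether the target population changes.

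Two other places describe matching differently. The Work package 1 Methods section says "Calendar quarter will be used as an exact matching variable within the propensity score matching process", and presents this as the route to the primary comparison. The Limitations section lists propensity-score matching, with multivariable modelling, as the protection against confounding and does not mention weighting. The Analysis section also plans subgroup analyses "to investigate heterogeneity in the impact of the telehealth intervention across socio-demographic groups".

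**The concern.** Matching on the propensity score and weighting by its inverse each remove measured confounding, but for different populations. Matching five comparators to each enrolled patient makes the comparators look like enrolled patients. Stabilised IPTW makes both arms look like the whole eligible cohort. The article does not name its estimand, but the description of the weighting implies the second target.

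Applying one method after the other therefore does not give the same analysis on fewer rows. The result depends on which propensity score supplies the weights, and neither choice reproduces the primary quantity in general. A gap between the fallback and the primary could not be read as a computing effect.

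The trigger and the label also conflict. A sensitivity analysis needs a main result to be compared with. This one is invoked when the main analysis cannot be run, and the article does not say what the primary estimate for emergency admissions would then be.

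**Working it through.** The plan gives no figure for the fallback, so there is nothing of its own to reproduce. It supplies the 5:1 ratio, the order of steps, stabilised weights and a planning relative risk of 0.85. Propensity slopes, share treated and effect gradients are my assumptions.

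**Algebra.** Let x be a standardised risk score with density f in the eligible cohort, and p(x) the propensity. Enrolled patients have density proportional to f·p. With close matching, comparators also have density f·p.

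*Reading 1: score refitted in the matched set.* One enrolled patient to five comparators gives p ≈ 1/6 = 0.167 for everyone. The stabilised weights are (1/6)/(1/6) = 1 for enrolled patients and (5/6)/(5/6) = 1 for comparators. Both arms stay at f·p, so the estimate is the effect in enrolled-type patients.

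*Reading 2: full-cohort score carried over.* Enrolled patients: f·p × 1/p = f. Comparators: f·p × 1/(1−p) = f·p/(1−p). With a logistic propensity of slope b, p/(1−p) is proportional to exp(bx). If x is standard normal, the weighted comparator mean is b and the weighted enrolled mean is 0, so the standardised difference is −b. Slopes of 0.5, 0.8 and 1.2 give −0.50, −0.80 and −1.20. Stabilisation multiplies each arm by a constant and does not change this.

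**Simulation.** 200,000 to 400,000 eligible patients, two confounders, additive DiD on quarterly admission rates, four replicates per scenario. Main scenario: 3.6% treated, slope 0.6 on each confounder, effect varying with risk. The true effect is -0.0201 in the whole cohort and -0.0399 in enrolled patients.

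| Analysis | Standardised differences | DiD |
|---|---|---|
| Crude | +0.59 / +0.59 | -0.0455 |
| Full-cohort IPTW (primary) | 0.00 / 0.00 | -0.0201 |
| 5:1 matched, unweighted | +0.01 / +0.01 | -0.0394 |
| Matched, refitted score | 0.00 / 0.00 | -0.0389 |
| Matched, full-cohort score | -0.59 / -0.58 | -0.0140 |
| Random 5:1 comparators, full-cohort score | 0.00 / +0.01 | -0.0202 |

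In the refitted row the scores ran from 0.158 to 0.175 and the weights from 0.95 to 1.06.

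Other scenarios:
- *Weaker selection (slope 0.3):* refitted -0.0302, against true values of -0.0201 (cohort) and -0.0294 (enrolled); full-cohort score, standardised differences -0.30 / -0.30.
- *About 12% treated, where good matches run short:* refitted weights range from 0.30 to 5.62 and the estimate is -0.0259, between -0.0201 and -0.0366.
- *Matching on only one of the two confounders, then refitting on both (main scenario):* balance is restored, but the DiD is -0.0323, still not the primary quantity.
- *Constant rate ratio of 0.85:* on the additive scale, refitted -0.0214 against true values of -0.0164 (cohort) and -0.0220 (enrolled). On the ratio scale the effect is 0.85 in every population, so the two would agree.

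**Rate-ratio scale with heterogeneity.** Assume log RR = −0.10 − 0.10x, 2–15% treated and slopes 0.5–1.2. If baseline log rates rise 0.5 per SD of risk, the cohort RR is exp(−0.10 − 0.10×0.5 + 0.005) = 0.87, and the enrolled-type RR is 0.78–0.83. With no baseline gradient the figures are exp(−0.10 + 0.005) = 0.91 and 0.81–0.87.

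**The case against.** The strongest defence has four parts.

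1. Matching before the weighting approach most naturally means that the treatment model is fitted in the matched cohort. That gives a balanced and valid estimate for its own population. This stands, and it is why the change of population, not the reversed imbalance, is the main point.
2. If full-cohort weights were carried over, the balance, overlap and effective-sample-size checks in the same section should show the problem. This also stands, though the section gives no remedy for that case.
3. The size of the population shift rests on an effect gradient that the article does not state, and a constant rate ratio would remove it on the ratio scale. Correct. But the plan sets out to look for heterogeneity, so it cannot take a constant ratio for granted.
4. The fallback is optional and conditional, and an article may leave the choice of score to the analysis plan. The choice of score may be left there. The sequence, trigger and label, however, are fixed in the article, and a plan that follows them inherits the problem.

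A reader might infer more: that the fallback will bias the primary outcome, that it can check nothing, that it formally replaces the primary analysis, or that it is likely to be used. The documents support none of these. They do not say that full-cohort weights are carried over, a balanced estimate in enrolled-type patients is still informative, the fallback is never called a replacement, and no computing limit is stated.

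**Conclusion.** The point holds in a limited form. The fallback is not a purely computational variant of the primary IPTW-DiD. On the natural reading it estimates the effect in enrolled-type patients. It will differ from the primary when effects vary with risk, and agree on the ratio scale when the rate ratio is constant. On the less natural reading it reverses the measured imbalance. Whichever score is used, the article defines no primary estimate for the case in which the full cohort cannot be run. It also contradicts itself on whether matching belongs to the primary analysis (Methods and Limitations) or is only a contingency (Analysis).

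The sizes (for example -0.0389 against -0.0201, or 0.78–0.83 against 0.87) are illustrations under assumed propensity and effect gradients, not predictions. In every scenario with a varying effect, the refitted estimate moved from the whole-cohort effect towards the effect in enrolled patients. Weights close to 1 require enough comparators for close matching. A comparison cohort large enough to trigger the fallback makes that plausible.

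**What to change.** In the Work package 1 Analysis section, replace the fallback. If the untreated cohort is too large, draw a random sample of untreated patients, stratified by index quarter and locality, and record the sampling fractions. Multiply each sampled patient's full-cohort IPTW weight by the inverse of the fraction. State that this is the primary analysis if the full cohort cannot be run. Propensity matching would itself need a score for every candidate comparator, so this asks for no additional modelling. The simulated random sample used one fraction throughout, which cancels in weighted means, so the inverse fraction was not needed there. It is needed once fractions differ between strata.

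If 5:1 matching is kept, analyse the matched set without full-cohort IPTW weights, label it the effect in enrolled patients, and do not present it as a computational check.

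In either case, reconcile the Methods and Limitations sections with the Analysis section on whether matching is part of the primary analysis.

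The cost is a few sentences of text and a small loss of precision from sampling comparators, which the sampling fraction controls.

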### Methods

Using a prospective study of 2,000 patients accessing MCTS and a comparison group of 2,000 who declined the service. We will gather survey data from telehealth patients on various health metrics, at 1-and 12-weeks post-enrolment, and we will contact patients, monthly, who have recently declined to use the service and collect baseline data and 12-week follow-up data for comparison.

The survey will include measures of health-related quality of life (EQ-5D-3L); Patient Health Questionnaire-9 (PHQ-9); Generalised Anxiety Disorder Questionnaire (GAD-7); Digital Health Literacy Scale (Nelson et al., 2022), and using MCTS standard survey questions, collect information on telehealth care support, patient satisfaction and evaluations on care quality and communication with healthcare professionals. Demographic information for MC telehealth patients is routinely collected. Thus, the survey for the comparator group will gather the following demographic information: health conditions (COPD, HF, and diabetes), age, sex, ethnicity, postcode, English language fluency, number of people living in the household, and reasons for declining the telehealth service for the comparison group to analyse deprivation indices. Our survey questions were based on those used by the Office for National Statistics (Office for National Statistics, 2023).

Our intervention group survey sample size is based on the size of the population of interest (people using the telehealth service), the level of confidence, and the degree of margin of (random) error. Our population is the approximately 22,000 patients who have used the MCTS. With a confidence level of 95%, a sample of 2,000 telehealth patients would provide a margin of error between 2% and 3% in how the responses would represent those of the total population. We feel that this is an acceptable margin of error. For a margin of error of 3% we would require 1,018 responses and so this allows for sufficient loss to follow-up from the target 2,000 participants. As such we require a similar size in the comparator group.

The inclusion criteria for the intervention group comprise patients who are receiving the MCTS and have a diagnosis of COPD, diabetes and/or HF. The comparison group consists of eligible patients who have declined telehealth services. Exclusion criteria for both groups include not having the aforementioned diagnoses, ineligibility for receiving MCTS, lack of mental capacity to consent, opting out of research, or not consenting to participate. Patients who decline telehealth may differ systematically from those who accept the service and will therefore not be considered a fully unbiased comparator group. Differences may include digital confidence, health literacy, illness perceptions, perceived burden of monitoring, social support, deprivation, language, disability, clinical severity, and previous experiences of healthcare. Baseline characteristics of accepters and decliners will be compared. Propensity weighting, matching or covariate adjustment methods will be used to reduce observable imbalances. Reasons for declining will be reported where available.

The comparator group will be recruited using the MC ‘Count Me In’ system (Bifarin et al., 2025; NHS Mersey Care, 2025). The ‘Count Me In’ system is an initiative to facilitate the involvement of patients in research. All patients can opt-out of the ‘Count Me In’ system. The research opportunity and participant information sheet will be provided in accordance with potential participants’ preferred method of contact.

For the intervention group, the survey forms part of routine practice and is administered through Docobo Ltd until March 2026; starting in April 2026, the Luscii system is used (NHS, 2025) thereafter (see MCTS section above). For the comparison group, the survey can be completed digitally (Jisc Online Surveys, i.e., https://app.onlinesurveys.jisc.ac.uk/login), by post or over the telephone. Where participants are completing the survey by telephone, researchers will input their answers on Jisc Online Surveys in real time on their behalf. Where participants are completing the survey by post, their answers will be recorded onto Jisc Online Surveys. Following data collection, data will be removed from Jisc Online Surveys and pseudo-anonymised for analysis.

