MCTS is a complex, clinician-led intervention and variation may occur in monitoring intensity, alert frequency, escalation activity, and staff contact. A team of registered nurses (Band 6–8a) (NHS England, 2024b) and healthcare assistants monitor patient data daily. Alerts are generated using individualised, National Institute for Health and Care Excellence (NICE)-aligned thresholds based on physiological readings, symptoms, or missing data. All alerts are reviewed by the telehealth team and may prompt telephone assessment, self-management advice, referral, or escalation to urgent or emergency care, ensuring a clinician-led rather than fully automated response. Senior clinicians can also set individual thresholds when it makes sense to do so. Healthcare assistants check on patients who do not send in their readings and triage patient calls. Administrative staff support non-clinical activities such as enrolling patients onto the system (Mersey Care NHS Foundation Trust, 2025a; NHS England, 2025c). Patients receive written and video educational resources at enrolment. Patient-reported outcomes, including quality of life, medication adherence, mental health, self-management, and service use, are collected through online questionnaires. Communication is primarily via the app, with telephone contact used when required. Formal fidelity monitoring was not routinely collected; therefore, fidelity will not be formally evaluated. Where available, service activity measures will be reported descriptively to provide context on intervention delivery.

The MCTS was implemented incrementally across localities, conditions and platform configurations. This phased rollout is important for interpreting both service reach and the construction of comparator groups. A map illustrating the phased geographical rollout of MCTS is provided in Table 1 which summarises key changes in geography, eligibility, case finding, commissioned capacity, and platform use over the study period.

**Table 1 TB1:** Timeline of MCTS rollout, eligibility criteria and platform transitions.

Metric	Liverpool	Sefton	St Helens	Wirral	Cheshire West
Monitoring established date^*^	November 2017	July 2022	September 2021	May 2023	February 2024

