### Analysis

Appropriate longitudinal analysis will be conducted using ANOVA and multilevel modelling (via R software or SPSS v26) to assess differences in self-reported outcomes between the telehealth intervention group and the comparator group. Key outcomes include adherence, digital health literacy, satisfaction with care, mental health indicators, and service use for primary and secondary care. Additionally, subgroup analysis will explore survey responses based on sociodemographic factors such as place, deprivation, ethnicity, age, and sex.

**Work package 3:**  *To interview patients and staff and understand the barriers and enablers of effective service delivery care*

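### In WP2 the way the survey is completed differs between users and decliners, and a direct week-12 comparison would mix any mode effect with the group difference; recording mode and analysing change largely removes it

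*Protocol article*

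**What the plan says.** The Protocol article describes the two groups' surveys differently.

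- **Users.** Under Work package 2, Methods, the only route named is the service's own system: "the survey forms part of routine practice and is administered through Docobo Ltd until March 2026; starting in April 2026, the Luscii system is used". The section on the Mersey Care Telehealth Service agrees: "Patient-reported outcomes, including quality of life, medication adherence, mental health, self-management, and service use, are collected through online questionnaires".
- **Decliners.** The same Methods section offers three routes: Jisc online, post and telephone. On the last it says: "Where participants are completing the survey by telephone, researchers will input their answers on Jisc Online Surveys in real time on their behalf". Postal answers are also transferred to Jisc.
- **Instruments.** Both groups are to be assessed with EQ-5D-3L, PHQ-9, GAD-7, a digital health literacy scale and the service's satisfaction questions. Users are surveyed at weeks 1 and 12, decliners at baseline and week 12.
- **Analysis.** ANOVA and multilevel models are to be used "to assess differences in self-reported outcomes between the telehealth intervention group and the comparator group". On outcomes it says: "Key outcomes include adherence, digital health literacy, satisfaction with care, mental health indicators, and service use for primary and secondary care".
- **Adjustment.** Weighting, matching or covariates are planned for observable differences between accepters and decliners. Mode of completion is not named there, in the WP2 analysis, or under Limitations of the study.

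**The concern.** Questions on depression, anxiety and satisfaction may be answered differently when spoken to a researcher than when completed privately. Telephone and post are described for one group only, so any such difference falls on one side of the comparison.

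Balancing the groups on patient characteristics does not remove it, because mode is a feature of how the outcome is measured and not of who the patient is. Nothing in the article asks a decliner to keep the same mode at both waves, so a switch between baseline and week 12 could also enter the change score.

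At stake is the reading of small differences. With 1,000 to 2,000 people per group, a small systematic shift can reach statistical significance. If mode is not recorded when the answers are taken, no later analysis can recover it.

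**Working it through.** **1. The plan's own figure.** For a 3% margin at 95% confidence with a population of 22,000: n0 = 1.96² × 0.25 / 0.03² = 1,067.1, and n = 1,067.1 / (1 + 1,066.1 / 22,000) = 1,017.8, rounded up to 1,018. The stated 1,018 is reproduced. It concerns one proportion in one group and says nothing about mode. It is used below only as a plausible number of responders per group, alongside the target of 2,000.

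**2. Precision of a two-group comparison** (outcome in SD units, equal groups, two-sided 5%).
- SE = √(2/n): 0.0443 at 1,018 and 0.0316 at 2,000.
- Detectable with 80% power = 2.80 × SE: 0.124 SD and 0.089 SD.
- Just significant = 1.96 × SE: 0.087 SD and 0.062 SD.

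**3. Week-12 scores compared directly.** Let f be the share of decliners answering by telephone and d the shift from telephone completion. Neither is in the documents; assume f = 20-60% and d = 0.1-0.3 SD. Bias = f × d.
- Low: 0.2 × 0.1 = 0.02 SD.
- High: 0.6 × 0.3 = 0.18 SD.

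With no true difference, the chance of a significant result is Φ(bias/SE − 1.96) + Φ(−bias/SE − 1.96). For f = 25% and d = 0.2 SD, bias is 0.05 SD and the chance is 20% at 1,018 per group and 35% at 2,000, against a nominal 5%.

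**4. Change from the first survey.** If each person keeps the same mode and the shift is constant, d enters both scores and drops out. Bias is 0 and the error rate stays at 5%. If a net share g of decliners switches in one direction, bias = g × d. With g assumed at 10-20%:
- Low: 0.1 × 0.1 = 0.01 SD.
- High: 0.2 × 0.3 = 0.06 SD.

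Switches in opposite directions offset each other, so these values are upper limits for a given amount of switching. If the two waves correlate at 0.6 (assumed), the SD of change is √(2 × 0.4) = 0.894. The detectable difference in change at 1,018 per group is then 0.894 × 0.124 = 0.111 SD, and the largest switching bias is 0.06 / 0.111 = 54% of it. At g = 10% and d = 0.3 SD (bias 0.03 SD), the false-positive rate is 12% at 1,018 and 19% at 2,000.

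**5. Precision of a sensitivity analysis without telephone responses.** Detectable difference = 2.80 × √(1/n + 1/(n(1 − f))). At n = 1,018 and f = 20%: 2.80 × √(1/1,018 + 1/814.4) = 0.132 SD. At f = 60%: 2.80 × √(1/1,018 + 1/407.2) = 0.164 SD. Both compare with 0.124 SD for all responses, in week-12 SD units.

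**The case against.** The strongest reply is that the plan is longitudinal. The WP2 aim in the Introduction speaks of changes in the outcomes, both groups are surveyed twice, and the WP2 Analysis section names multilevel models. In that setting a stable mode shift cancels. This stands. A reader might infer that a bias of up to 0.18 SD is built into the WP2 result; the documents do not support that, because the figure needs a direct week-12 comparison, which the article does not rule out but which is not its natural reading.

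Second, every input on telephone share, shift and switching is assumed. That also stands: the article establishes that mode differs by group, not that scores are biased. It describes no practice of following up non-responders by telephone, so that cannot be cited as a source of switching.

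Third, a reader might infer that the bias will be largest in, and will distort, the equity subgroups. The planned WP2 subgroups are place, deprivation, ethnicity, age and sex. Digital confidence is not one of them, and nothing shows how telephone use would vary across them.

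Fourth, several routes are a defensible choice. The article itself expects decliners to differ in digital confidence, language and disability, and an online-only survey could exclude some of them. This is a reason to keep the routes.

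Fifth, a condensed article may leave a mode field and a mode rule to documents not shown. That is possible, and if they exist the point is met. It is still worth raising, because it concerns data that must be captured at collection.

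One might read the users' route as not strictly exclusive, since the word 'only' does not appear. However, the telephone-supported submission in the service description concerns physiological and symptom data, not this survey.

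**Conclusion.** The point holds in a limited form. As described, mode of completion is confounded with group in WP2, and the planned adjustment does not deal with it. Size and direction cannot be derived from the documents.

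Under the stated assumptions the bias runs from negligible to above the detectable difference (0.02-0.18 SD against 0.124 SD) if week-12 scores are compared directly. It falls to at most about 0.01-0.06 SD in change from the first survey, and to zero if each person keeps one mode and the shift is constant.

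This is a cheap improvement to data collection. It is not evidence that the WP2 comparison is invalid.

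**What to change.** - Keep all three routes for decliners.
- Record the mode of completion at each wave.
- Ask each decliner to use the same mode at baseline and week 12. Where that is not possible, accept the response and flag it.
- Base the group contrast on change from the first survey (week 1 for users, baseline for decliners).
- Report a sensitivity analysis limited to decliners' self-completed (online or postal) responses, and state that it selects the more digitally confident or literate decliners.

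Adding a telephone indicator to the model is not advised. Telephone completion is described only among decliners, so its coefficient would be estimated within that group alone and would absorb real differences in change among those who choose the telephone.

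The cost is one data field, one rule for survey staff and some flagged week-12 responses. The sensitivity analysis loses precision as shown in step 5 of the working.
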